## Abstract

**Background:**

Pre-diabetes is a growing health concern where a large percentage of these patients develop full type 2 diabetes. Effective interventions on pre-diabetes can prevent or delay the occurrence or development of diabetes. Pharmaco-dynamics and pre-clinical of JinQi-Jiangtang tablets (JQJT) suggest that it could be benefit for pre-diabetes.

**Methods/Design:**

Randomized controlled trial (RCT) is implemented in this study. The study term is 24 months (12 months for intervention and 12 months for follow up). Participants are recruited from four cities of China: Beijing, Tianjin, Xi'an and Nanning. Four hundred participants are randomized to treatment group (JQJT tablets) and control group (Placebo); two hundred participants each. People being included in this study must have been diagnosed as pre-diabetes via western medicine criteria and traditional Chinese medicine (TCM) criteria. The end-point indexes include: incidence of diabetes mellitus and reversion rate. Primary outcome indexes include: oral glucose tolerance test; insulin releasing test; glycosylated hemoglobin (HA1c). Secondary outcome indexes include: score of the Short Form 36 Health Survey Questionnaire (SF-36); score of TCM symptoms; blood lipid test. Indexes of safety include: general medical examination; blood and urine regular test; electrocardiogram (ECG), liver function (ALT) and renal function (BUN, Creatinine) test; record of adverse event, such as headache, faint, etc. Qualitative control will be implemented and a number of standard operating processes (SOPs) will be formed throughout the study: laboratory quality control measures; compliance control for researchers and participants; researcher training before study; supervision; investigational drug management and others.

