### Sample size

According to the results of the "JQJT tablets intervene IGT study" by Professional Committee of Diabetes, Association of Integrative Medicine in Tianjin, annual average tyoe 2 diabetes conversion rate of test group is 4.05%, control group is 12.69%. The sample was estimated according to the parameters: *α *= 0.05, *β *= 0.1

Considering attrition of no more than 20%, the total number of qualified cases in the groups will be 200 each (n = 400).

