##### Analysis of data sets

• Full analysis set: According to the principle of analysis for intention to treat (ITT), participants will be rejected by smallest and reasonable method. The last observation carried forward (LOCF) method will be used for the missing data supplement.

• Per-protocol set (PPS): PPS should be used in the patients who satisfied with the following characters: compliance is between 80% and 120%; not using prohibited drugs; fit with inclusion criteria; case of completed observation.

• Safety set (SS): All information of safety record will be assessed, including adverse events and laboratory test results.

• Statistical analysis method: Relative risk reduction (RRR), absolute risk reduction (ARR), number needed to treat (NNT) adopt nonparametric methods to evaluate the effectiveness. To adopt t-test, repeated measure analysis of variance, radit test, rank test, survival analysis, Cox proportional hazards regression model and so on.

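### The trial is sized on diabetes conversion, but the labelled primary outcomes are three other measures, and neither the confirmatory variable nor its time point is fixed

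*Protocol article*

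**What the plan says.** All references are to the protocol article.

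- **Labelled primary outcomes** (abstract, Methods/Design; same list under Primary outcomes): "Primary outcome indexes include: oral glucose tolerance test; insulin releasing test; glycosylated hemoglobin (HA1c".
- **A separate tier** (abstract; Index of end point under Outcome measures): "The end-point indexes include: incidence of diabetes mellitus and reversion rate". The body defines both items by glucose criteria and attaches no assessment time.
- **Sizing basis** (Sample size): "annual average tyoe 2 diabetes conversion rate of test group is 4.05%, control group is 12.69" percent, followed by "The sample was estimated according to the parameters: *α *= 0.05, *β *= 0.1" and "Considering attrition of no more than 20%, the total number of qualified cases in the groups will be 200 each (n = 400". No planning value is given for OGTT, insulin release or HbA1c.
- **Duration** (abstract): "The study term is 24 months (12 months for intervention and 12 months for follow up". Tables 1 and 2 record end-point events and OGTT monthly to month 12, then at months 14, 18 and 24. After screening, insulin release and HbA1c are measured only at months 12 and 24.
- **Analysis** (Analysis of data sets; Mathematical statistics analysis and expression): effectiveness is judged by RRR, ARR and NNT. Tests are listed by type of data, together with "survival analysis, Cox proportional hazards regression model and so on". No test level, order of testing, success rule or analysis period is given.

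**The concern.** Two parts of the article point to different confirmatory variables. The sample size and the effectiveness measures (RRR, ARR, NNT) fit an event, namely conversion. The label primary is attached to three glycaemic measurements that have no sizing basis. The end-point tier does not settle the matter, because it holds two variables with no order between them.

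The time point is also open. The planning rates are per year, while events are collected through a treated year and an untreated year.

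At stake is what the trial's confirmatory claim is. As written, a report could present conversion, reversion or a glycaemic measure, at 12 or at 24 months, as the planned main result, and a reader could not check that against the protocol.

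**Working it through.** **1. The plan's own sample size.** Inputs from Sample size: p1 = 0.0405, p2 = 0.1269, alpha 0.05, power 0.90, attrition 20%. The pooled formula for two proportions is

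n = [z(alpha)·√(2·p̄·q̄) + z(power)·√(p1·q1 + p2·q2)]² / (p2 − p1)²

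with p̄ = 0.0837. Two-sided: [1.960 × 0.3917 + 1.2816 × 0.3869]² / 0.0864² = 1.596 / 0.007465 = 213.8, so 214 per arm, and 214 / 0.8 = 267.5, so 268 after attrition. One-sided, the same formula gives 175 and 219. A one-sided arcsine calculation gives 164 and 205 (197 if inflated by × 1.2), which is close to the stated 200. Sidedness and formula are not stated, so I do not call 200 an error, and the point here does not depend on it. The calculation concerns conversion alone.

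**2. Familywise error.** Assumption: any single success at two-sided 0.05 would count, with no adjustment. For k independent tests the error is 1 − 0.95^k:

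- k = 2 (the two end points): 9.75%
- k = 3 (the labelled primaries): 14.3%
- k = 5 (all of them): 22.6%

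The variables are related, so equally correlated z-tests were simulated (400,000 draws):

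| Correlation | 3 tests | 5 tests |
|---|---|---|
| 0 | 14.3% | 22.6% |
| 0.3 | 13.6% | 20.9% |
| 0.5 | 12.5% | 18.4% |
| 0.7 | 10.9% | 14.8% |
| 0.9 | 8.3% | 10.1% |

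If all three primaries had to succeed, there would be no inflation.

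**3. Horizon.** Exact power of the uncorrected chi-square test, two-sided 0.05. The number analysed is 200 × 0.8 = 160 per arm after the stated attrition, or 200 without loss. Assumption: the control rate is 12.69% in each year, so control risk at month 24 is 1 − 0.8731² = 23.8%. Drug-arm risk at month 24 is 1 − 0.9595 × (1 − r), where r is the assumed year-2 rate off drug:

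| Scenario | r | Drug vs control | RR | Power, 160 per arm | Power, 200 per arm |
|---|---|---|---|---|---|
| Month 12 | – | 4.05% vs 12.69% | 0.32 | 82% | 89% |
| Month 24, no effect persists | 12.69% | 16.2% vs 23.8% | 0.68 | 39% | 48% |
| Month 24, half persists | 8.37% (midpoint of the two rates) | 12.1% vs 23.8% | 0.51 | 78% | 87% |
| Month 24, all persists | 4.05% | 7.9% vs 23.8% | 0.33 | 98% | 99% |

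The article gives no information on r. The same drug and the same sample size therefore give power anywhere from 39% to 98% at 160 per arm if the comparison is read at month 24, against 82% at month 12.

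**The case against.** The best defence is that the end-point tier was meant as the top tier. It is listed first, the trial is sized on conversion, conversion has its own evaluation criterion under Measure and evaluate tools, and RRR, ARR and NNT are event measures. On that reading the fault is poor labelling, and a multiplicity procedure may stand in an analysis plan that is not shown. The reading is plausible, but it does not close the gap: the top tier would still hold two unordered variables without a time, and the word primary would still be attached to three others. The article states both hierarchies, so this is a disagreement in its text and not detail lost in condensing.

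A reader might infer more than the text supports:

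- **That all five variables are tested at 0.05, so the stated alpha is not held.** The value 0.05 appears only as a sample-size parameter. No level is given for any test, and nothing says that one success is enough.
- **That every variable is tested at 15 post-baseline visits.** Only OGTT and end-point events have 15. Insulin release and HbA1c have two, and repeated-measures ANOVA is named for repeated data.
- **That a 24-month comparison must dilute the effect or break proportional hazards.** That follows only if the effect wanes off drug. If it persists, month 24 has more power than month 12. The article does not say that the Cox model covers 24 months.
- **That the independence figure of 22.6% is the expected error.** Reversion is defined partly by the 2-hour OGTT value, so the variables are linked. The figure is the upper end of the range shown.

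**Conclusion.** The point holds, and the plan is wrong as written here: the outcome labelled primary is not the one to which the alpha and beta apply, and no confirmatory time is fixed. The mismatch rests on the text alone and needs no assumption.

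The sizes are conditional. The error of about 8-14% for three outcomes and 10-23% for five assumes that any success counts, without adjustment, at correlations from 0.9 down to 0. The supportable statement is that control of the 5% error is not shown, not that it is lost. The month-24 power of 39% to 98% assumes 160 analysed per arm, constant control risk and an unknown off-drug effect. It shows that the choice of horizon is consequential, not that the longer one is worse.

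**What to change.** Name one primary endpoint, incidence of type 2 diabetes from randomisation through month 12, tested at 0.05 with the sidedness stated. This is the quantity the trial is sized on. Relabel reversion, OGTT, HbA1c and insulin release as secondary. Either test them in a pre-specified order chosen by the sponsor or report them as supportive, without confirmatory claims. Report months 14-24 as a separate off-drug analysis, not pooled with the treated year into one hazard ratio. Make the abstract, Outcome measures, Sample size and the analysis section agree.

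The cost is wording only, with no new visits or data. The three glycaemic measures lose primary status, and conversions after month 12 do not count towards the primary test. The change does not by itself deliver the planned 90% power: two-sided, month-12 power is about 82% with 160 per arm and 89% with 200. Keeping all five variables confirmatory by Bonferroni (0.05 / 5 = 0.01 each) would cost more. By the normal approximation, conversion power falls from 80.0% to 58.6% at 160 per arm, and 304 per arm (380 after 20% attrition) would be needed for 90%.

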**Discussion:**

The aim of this study is to evaluate the effectiveness and safety of JinQi JiangTang (JQJT) tablets for the treatment of patients with pre-diabetes.

**Trial registration:**

Chinese clinical trials register ChiCTR-TRC-00000401

## Background

An increasing number of people experience complications from symptoms of pre-diabetes. Some studies have discovered that about 5%-10% of pre-diabetes will develop into diabetes within one year and the occurrence of cardiovascular events in patients with pre-diabetes are higher than in healthy individual. According to Hoorn[1], the rates of development of diabetes after 5.8-6.5 years follow-up from patients with normal glucose tolerance, single impaired fasting glucose (IFG), single Impaired Glucose Tolerance (IGT), both IGT and IFG people are 4.5%, 33.0%, 33.8% and 64.5%, respectively. Therefore, the prevention of type 2 diabetes in pre-diabetic patients is a topic of importance in diabetes research.

### Progress of pre-diabetes

Effective interventions on pre-diabetes can prevent or delay the occurrence or development of diabetes; it can also reduce micro-vascular and macro-vascular complications. The result of the Daqing study from 1986-1994 concluded that lifestyle interventions could reduce the incidence of diabetes by 30%-50%[2]. However, another study confirmed that lifestyle interventions were not completely effective to prevent the development of type 2 diabetes for high-risk groups[3]. Another study showed a high trend of body weight rebound and blood glucose increase after 1-2 years of lifestyle interventions [4]. STOP-NIDDM discovered that IGT intervention was able to reduce the occurrence of diabetes by 36% [5]. DPP discovered that metformin and troglitazone can significantly reduce the risk of diabetes [6]. In the TRIPOD study, troglitazone reduced the risk of diabetes by 55% in gestational diabetes patients [7]. The latest DREAM trial showed that the intervention of pre-diabetes can delay the disease process [8,9]. These studies give us hope to prevent diabetes effectively.

### Prevention and treatment on pre-diabetes in traditional Chinese medicine (TCM)

Traditional Chinese medicine (TCM) can treat pre-diabetes effectively[10]. A systematic evaluation of pre-diabetes intervention, including 19 randomized controlled trials, showed that the combination of Chinese medicine and lifestyle intervention can decrease fasting blood glucose in 1471 cases. Meanwhile, the 2 hours postprandial blood glucose and 2 hours postprandial insulin levels were lower than a simple lifestyle intervention [11]. Zhou Zhuoning[12]considered that diabetes can be explained by three TCM Syndrome from IGT to diabetes as: yin deficiency with heat, dual deficiency of yin and qi, dual deficiency of yin and yang in development.

### Constituents of JQJT tablets

Alkaloid is the major constituent of Coptis, including Berberine, palmatine, methyl and coptisine. Berberine is the most content among them (accounting for 6.88%~13.64%). The main chemical constituents of Astragalus is flavonoids, saponins and polysaccharides. The main chemical composition of Honeysuckle is volatile oils, flavonoids, organic acids and other substances, chlorogenic acids compound is the main active ingredient among them. Berberine, flavonoids can lower blood sugar significantly and chlorogenic acids compounds can strengthen the immune system.

### Pharmaco-dynamics of JinQi-Jiangtang(JQJT) tablets

• JinQi-Jiangtang (JQJT) tablets is composed by Coptis, Astragalus, and Honeysuckle.

• Influence on glycometabolism: Studies before proved that JQJT tablets can improve mice glucose tolerance obviously[13]. Honeysuckle can decrease blood sugar[14]. Berberine, as a natural plant alkaloid isolated from the Coptis chinens, has been noted for its potential glucose lowering effect[15].

• Influence on insulin resistance(IR) and serum insulin: JQJT tablets can improve the insulin resistance caused by Hydrocortisone and decrease the serum insulin in mice[16].

• Influence on immune function: JQJT tablets can improve immune function and protect thymus gland atrophy of mice [16].

### Pre-clinical of JQJT tablets

Sheng zhufang proved that JQJT tablets can improve insulin resistance in humans[17]. Gu wenyuan indicated that combination of JQJT tablets and Gliclazide can improve fasting blood-glucose (FBG) of 2 type diabetes patients[18]. Zhang rongrong discovered that JQJT tablets can not only prevent the progression from pre-diabetes to diabetes but also delay development of diabetic nephropathy (DN)[19].

## Methods/Study design

### Objectives

To evaluate the effectiveness and safety of JQJT tablets for pre-diabetes in China by comparison with placebo.

### Research type

Randomized controlled trial (RCT).

### Screening of participants

400 pre-diabetes patients will be divided into the treatment group and the control group (1:1). Participants should be included according to diagnosis criteria and inclusion criteria (reference to the next section).

### Intervention

• Arrangement for intervention: All researchers in this study will be trained before their participation. Some measures will be implemented in order to ensure compliance, such as compensation and prize. Patient handouts will be delivered to every participants to instruct their medication and cooperation.

• Lifestyle intervention: Researchers will develop an individual diet program for each participant, including reasonable match of calories, protein and carbohydrates, low-salt and low-sugar diet, advise them to give up some bad diet habits. Risk factors, such as smoking and alcoholics, will be controlled strictly. Individual's exercise program will be formulated for all participants according to their age, gender, etc.

• Drug intervention: The period of drug intervention is 12 months. All participants have to visit researchers every month. The interventions are as follows: JQJT tablet for treatment group, taking seven tablets each dose and twice daily, all the drugs are taken before meal; Placebo of JQJT for control group, the method and time of taking drugs is the same as treatment group.

### Randomization

The randomization of the trial will be completed by the independent data center named Interact Voice Responding System (IVRS). According to a random sequence table (generated by SAS8.2), participants who satisfied the inclusion criteria will be allocated randomly into one of the two groups with a ratio of 1:1. The identification code and random number, which is unique for each participants, will be generated by the IVRS.

### Allocation concealment

All researchers will receive training of allocation concealment at the central randomization office. The randomization sequence schedule is held and controlled by the appointed one who is not involved in this trials. The schedule is secret for researchers, participants and other research personnel before study, so allocation sequence is implemented in a secure manner to prevent foreknowledge by either of them.

### Blindness

Double-blinding method is adopted in this study. Simulated agents of JQJT tablet have the same appearance, shape, color and packaging with JQJT tablets, so researchers and participants can not know the kind of medication and group.

Twice unblinding method is adopted in this study. Firstly, after close of data-base, the one who keep the blind code will deliver a allocation schedule only signed with group A and B to statistics department. Secondly, after the handing of statistical outcome and final report, the one keeping the blind code will declare real meaning of group A and B. In case of emergency during this trials, the blinding will be broken after obtaining the consent of principle investigator.

### Sample size

According to the results of the "JQJT tablets intervene IGT study" by Professional Committee of Diabetes, Association of Integrative Medicine in Tianjin, annual average tyoe 2 diabetes conversion rate of test group is 4.05%, control group is 12.69%. The sample was estimated according to the parameters: *α *= 0.05, *β *= 0.1

Considering attrition of no more than 20%, the total number of qualified cases in the groups will be 200 each (n = 400).

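### The Sample size inputs and the 200 per arm do not fit together: a standard two-sided calculation gives about 80% power at 20% attrition and about 88% with none, not the stated 90%

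*Protocol article*

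**What the plan says.** The Sample size section of the protocol article takes its rates from an earlier study of the same product in people with IGT: "annual average tyoe 2 diabetes conversion rate of test group is 4.05%, control group is 12.69"%. It then gives the error rates, "The sample was estimated according to the parameters: *α *= 0.05, *β *= 0.1", and the resulting number, "Considering attrition of no more than 20%, the total number of qualified cases in the groups will be 200 each (n = 400").

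Two other places show that 400 is the number entering the trial. The abstract says "Four hundred participants are randomized to treatment group (JQJT tablets) and control group (Placebo); two hundred participants each", and Screening of participants says "400 pre-diabetes patients will be divided into the treatment group and the control group (1:1"). The 200 per arm is therefore the figure before attrition.

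Under Mathematical statistics analysis and expression, the chi-square test is assigned to count data in general. The Sample size section gives no sidedness, formula, time horizon or number before the attrition allowance.

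**The concern.** Two event rates, an alpha, a beta and an attrition allowance determine a sample size once the test is chosen. Here the printed set can be checked, and under the usual choice (two-sided, two proportions) the printed number is well below what the printed beta requires.

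Beta is the risk of missing an effect as large as the one planned for. If that risk is about 20% at the attrition the plan itself allows for, and not 10%, readers weighing a non-significant result would credit the trial with more sensitivity than it has. The word *qualified* adds to the uncertainty, since it could be read as the number left after attrition.

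**Working it through.** **Inputs.** From Sample size: p1 = 0.1269 (control), p2 = 0.0405 (test), alpha = 0.05, beta = 0.1, attrition up to 20%, 200 per arm. From the abstract and Screening of participants: 400 randomised, 1:1. Assumptions: two-sided test, one-year rates.

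**Quantities used below.**
- Difference: 0.1269 − 0.0405 = 0.0864; squared, 0.007465.
- Mean rate: 0.0837. Pooled term √(2 × 0.0837 × 0.9163) = 0.3917.
- Unpooled term √(0.1269 × 0.8731 + 0.0405 × 0.9595) = √0.14966 = 0.3869.

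**Step 1: trying to reproduce 200 at beta = 0.1.** Pooled formula: n = (z_alpha × 0.3917 + z_beta × 0.3869)² / 0.007465.
- With z_alpha = 1.960 and z_beta = 1.2816: (0.7676 + 0.4958)² / 0.007465 = 213.8 per arm. Divided by 0.8, this is 267.3.
- Unpooled: (1.960 + 1.2816)² × 0.14966 / 0.007465 = 210.7 per arm. Divided by 0.8, this is 263.3.
- Rounded up before and after the allowance: 214 → 268 and 211 → 264.
- Arcsine: 202 → 253. With continuity correction: 237 → 297.

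None of these gives 200.

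**Step 2: what does give 200.** With z_beta = 0.8416 (beta = 0.2), the pooled formula gives (0.7676 + 0.3256)² / 0.007465 = 160.1, and 160.1 / 0.8 = 200.1.

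**Step 3: power of the stated design.** Power = Φ[(0.0864 × √n − 0.7676) / 0.3869].

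| Evaluable per arm | Attrition | Normal approximation | Exact, chi-square |
|---|---|---|---|
| 160 | 20% | 80.0% | 81.8% |
| 200 | 0% | 88.0% | 89.3% |

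The type II error is thus about 20% at the full allowance and about 12% with no loss, against the stated 10%.

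**Step 4: other readings, all at 90% power, per arm evaluable → randomised.**
- One-sided 0.05, pooled: 175 → 219. Power is 87.7% at 160 and 93.2% at 200 with no loss.
- One-sided 0.05, arcsine: 164 → 205.
- One-sided 0.05, log-rank (Schoenfeld), one year: 161 → 202 with the rate ratio as hazard ratio; 149 → 187 with the hazard ratio derived from the logs of the event-free proportions.
- Two-sided log-rank (Schoenfeld), one year: 197 → 246 and 179 → 224 on the same two definitions.
- Two-sided, annual rates carried over 24 months (23.8% vs 7.9%): 110 evaluable, or 137.5 after dividing by 0.8. Power at 160 is 97.5%.

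**Step 5: optional sensitivity to the control rate.** Same relative risk (0.0405 / 0.1269 = 0.319), 160 per arm, two-sided, normal approximation throughout: 69% at a control rate of 10%, 56% at 7.5%, 40% at 5%.

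**The case against.** **The calculation may rest on choices the article does not print.** It is a condensed account, and two-sided is no more stated than one-sided. One-sided arcsine (205 per arm) and one-sided log-rank (187 to 202) come close to 200 at beta = 0.1. The analysis section also lists survival analysis and Cox regression, and end-point events are recorded at every visit, so the chi-square test is not tied to this endpoint. This stands as a limit on what can be concluded. It does not make the printed figures consistent under the standard two-sided two-proportion calculation, and a one-sided pooled test also falls short at 160 per arm. The 24-month horizon does not explain 200 either: it would call for far fewer, and it needs the effect to last a year beyond the end of treatment, which the section does not claim.

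**80% is the floor.** The attrition allowance is an upper limit, and the full analysis set carries last observations forward, so dropouts are not simply removed. This is fair, and the power should be given as a range. But even with all 200 counted, the two-sided two-proportion figure is 88% (exact 89%).

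**Two stronger readings are tempting.** A reader might infer that beta = 0.2 was used and 0.1 is a misprint. The match at 200.1 suggests it, but without sidedness or formula the document does not show it.

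A reader might also infer that the 12.69% control rate is an error, because the Background says "about 5%-10% of pre-diabetes will develop into diabetes within one year" and all participants receive a lifestyle programme, which the article elsewhere credits with effect ("lifestyle interventions could reduce the incidence of diabetes by 30%-50"%). The document does not support that:
- The Background also reports 64.5% over 5.8 to 6.5 years for combined IFG and IGT, roughly 15 to 16% a year, and the diagnosis criteria allow for IFG and IGT together.
- It does not say that the 5 to 10% is free of lifestyle effects.
- The article does not say whether the study behind the 12.69% included a lifestyle programme.
- Planning on a named earlier study of the same product is a legitimate choice.

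**Conclusion.** The point holds as an inconsistency among the printed inputs. With 4.05% against 12.69%, two-sided 0.05 and beta 0.1, about 211 to 214 evaluable per arm are needed (about 263 to 268 randomised), against 200 randomised. The stated design has about 80% power at 20% attrition, rising to about 88% with none. This rests on a two-sided two-proportion test, one-year rates, and 200 as the number randomised. The last is supported by the abstract and Screening of participants; the first two are the conventional reading and are not stated. Which input is wrong cannot be settled from the article. The control rate is a planning assumption and no part of the error.

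**What to change.** In the Sample size section:

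1. State the sidedness, the formula and the time horizon behind the 200.
2. Unless these show another basis, restate the power. For example: with 400 randomised (200 per arm), a two-sided 5% comparison of one-year conversion rates of 4.05% and 12.69% has about 80% power if 20% are lost (160 evaluable per arm) and up to about 88% if none are lost, by normal approximation.
3. Say that 200 per arm is the number randomised, and drop the word *qualified* or define it.

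Optionally, show the power at lower control rates as a sensitivity figure, by the same method as the main figure (69%, 56% and 40% at 10%, 7.5% and 5%, with the same relative risk and 160 per arm).

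The cost is wording only. No participants are added and the conduct of the trial is unchanged. The stated power becomes less favourable.
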